##### Process data

**Session checklists** The fidelity of the ConquerFear treatment protocol will be assessed through a review of each session by the psychologists administering the treatment. This will be completed using session checklists included in the ConquerFear protocol. The checklist will be completed at the end of each session.

**Referral rates, uptake, and patient adherence** Feasibility (i.e., the extent to which *Fear-Less* can be successfully implemented to treat FCR [37]) will be assessed by collecting the FCR screening rates, referral rates for each intervention, and intervention uptake and adherence. In particular, the data collected will include the number of survivors: screened, referred to each intervention, declining participation (including reasons), completing measures, and the proportion of the intervention completed (either self-reported percentage of the self-management intervention completed or psychologist reported number of ConquerFear sessions completed). This will be collected using a screening log and case-report form (CRF).

For a list of study measures and process data, see Table 1.

**Table 1 Tab1:** Study measures

Time point		Pre-enrolment	At enrolment	Post-intervention
**Screening**	FCRI-SF	x		x
	FCR1	x		x
**Survivor experiences**	Screening Survivor Experiences Survey		x	
	Self-Management Survivor Experiences Survey			x
	ConquerFear Survivor Experiences Survey			x
**Process data**	Number of survivors screened	x		
	Number of survivors who declined screening	x		
	Number of survivors referred to each intervention	x		
	Number of participants that consented to the intervention		x	
	Number of survivors declining participation	x		
	Proportion of intervention completed			x
	Number of survivors who completed screening post-intervention			x
	Number of survivors who completed the evaluation			x

#### Study interventions

##### Fear-Less self-management intervention

The self-management intervention is a purpose-designed booklet adapted from a version developed for the evaluation of *Fear-Less* amongst Stage IV melanoma survivors treated with immunotherapies and targeted therapies [32].

The process for adapting the booklet included the following:Editing for applicability to a population treated for early-stage cancer.Review within a focus group with cancer survivors with a range of diagnoses to inform content and design.A review process by the Peter Mac Health Communications Manager and two members of the Peter Mac Consumer Literacy Education and Evaluation Group for feedback regarding the booklet’s design and language.

The feedback provided in steps 2 and 3 informed the development of the final version of the booklet. The self-management booklet includes psychoeducational material about FCR, information about healthy living and wellbeing, and key cognitive behavioral strategies to help address thoughts and behaviors that trigger and maintain FCR. These strategies include identifying triggers for FCR, clarifying values, goal-setting, relaxation, identifying unhelpful thoughts, focusing on things within one’s control, and developing a FCR management plan. As per the initial *Fear-Less* study [32], participants will read the booklet over 5 weeks.

On receipt of the booklet, participants will be provided with education on how to use the booklet, and an opportunity to ask any questions, by a member of the research team. Approximately, 3 weeks after receipt of the self-management booklet, the participant will be contacted by a member of the project team to provide phone support and further education as needed to support participants in using the self-management resource. As per the initial *Fear-Less* study, it is expected the clinician time taken for each of these phone calls will be approximately 20 min [32].

##### ConquerFear

ConquerFear consists of five individual sessions that promote value-based goal setting and teach survivor strategies to manage worry and excessive FCR. Each session will be approximately 60 min every 1–2 weeks and will be facilitated by a psychologist face-to-face or via telehealth. Each session is accompanied by home-based practice of skills learned in session and home reading to consolidate skill acquisition.

In Session 1, a FCR-specific assessment will be conducted and the model of FCR on which the treatment program is based will be introduced [18]. Discussion of existential changes brought about by cancer will be introduced as well as value clarification and goal-setting tasks to be completed for homework.

In Session 2, the impact of vulnerability factors (e.g., past traumatic life events) on the interpretation and meaning of FCR will be discussed. The rationale for the practice of Attention Training Technique (ATT) will be discussed, which aims to help patients reduce their rumination and shift their attention more flexibly when thoughts of recurrence occur. Clients will be asked to practice ATT daily throughout the remainder of the intervention.

In Session 3, Detached Mindfulness will be introduced. This is designed to enhance meta-cognition awareness and the ability to become an objective observer of thought content without evaluating or reacting to cognitions.

In Session 4, information about possible symptom recurrence will be provided and guidelines to help participants distinguish those from benign physical complaints. Self-examination practices and medical surveillance will be reviewed. Avoidant or excessive behaviors will be identified, and a behavioral contract to help clients engage in recommended levels of self-examination and follow-up tests will be developed. Beliefs that may underpin FCR will also be explored through Socratic dialog.

In Session 5, the goal-setting task will be reviewed, as well as skills learned during the intervention. A relapse prevention plan will be developed.

#### Study procedures

Over a 15-week period, eligible survivors who have completed screening will be invited to participate in the *Fear-Less* program. Survivors who provide consent to participate will be stratified into a specific level of care within the stepped-care program based on their screening score on the FCRI-SF [35, 38, 39].

Participants identified as experiencing low FCR (score of <13 on the FCRI-SF) will continue with their usual care with their medical and nursing teams. No further follow-up or additional screening will be undertaken for these participants.

Participants identified as experiencing moderate/subthreshold levels of FCR (score of 13–21 on FCRI-SF) will have a brief discussion with a psychologist on the research team to confirm they are concerned about their level of FCR and would like support for it. Participants who agree to proceed will be offered the clinician-guided self-management intervention.

Participants identified as experiencing high/clinical levels of FCR (score of ≥22 on the FCRI-SF) will have a brief discussion with a psychologist on the research team member to confirm the severity of FCR and whether they would like support for it. Factors that will be assessed during this discussion will include the frequency, emotional impact, functional impact, and avoidance of FCR. Participants whose assessment indicates clinical levels of FCR will be offered ConquerFear. Participants who are considered to have sub-threshold FCR, or who do not wish to take part in the ConquerFear therapy, will be offered the self-management intervention.

Following each intervention, participants will complete the screening questionnaires and a survivor experiences survey relevant to the intervention they received. To minimize missing data, questionnaires and surveys not returned within 2 weeks of receipt will be followed-up by phone and mail/email up to three times, at 2-week intervals. Options for follow-up treatment will also be discussed depending on the survivors’ needs. This may include no further treatment, or referrals to services such as a psychiatrist, additional individual therapy, or peer supports.

The three levels of interventions are summarised in Fig. 1.

**Fig. 1 Fig1:**
[figure not shown]
The *Fear-Less* stepped-care model

#### Safety reporting

The potential for adverse events is deemed to be low in this study. In the event that a member of the study team observes significant distress during their interaction with a survivor, a referral to a psychologist, psychiatrist, or other relevant healthcare professional will be offered. The survivor’s intervention can continue or be aborted depending on the response of the participant. If any disclosures of risks to safety (e.g., suicidal ideation) occur during any stages of the study, standard clinical processes will be followed including safety planning with the participant, and when needed advising an appropriate support person such as a member of the participant’s treating team and/or a family member. This limit to confidentiality is included in the consent form.

The sponsor and ethics department will be notified immediately of any safety issues and the management of these, respectively.

### Evaluation of Fear-Less by clinicians

#### Participants

Clinical staff working in the breast, gynecology, and head and neck clinical services will be invited to evaluate the *Fear-Less* program. These clinical staff may include nurses, oncologists, psychosocial oncology staff, and allied health staff.

##### Sample size

All clinical staff involved in the *Fear-Less* program will be invited to participate. It is anticipated that ten staff will be invited.

##### Recruitment and consent

Staff will be invited to provide feedback regarding their experiences with the program via an online survey. Staff will be emailed a link to the survey towards the end of the *Fear-Less* program evaluation period. It is anticipated this will occur in the last 1 to 2 weeks of the recruitment period and continue until the final participant has completed their intervention. Consent is implied by completion and return of the questionnaire.

#### Study measures

##### Staff evaluation survey

The extent to which *Fear-Less* is acceptable for clinicians will be assessed using the *Staff Evaluation Survey* (see Additional File 2), a purpose developed 10-item measure assessing each staff member’s involvement in the program and includes open-response items requesting positive and negative feedback. This survey was adapted from our earlier study evaluating *Fear-Less* among survivors with stage IV melanoma [32].

##### Process data

To further assess feasibility, the CRF will be used by the project team to record the time taken (in minutes) to deliver each component of the intervention and follow-up care (e.g., follow-up phone calls and referrals following intervention).

### Data management

Data will be entered and managed through REDCap [40, 41] and stored securely in password-protected folders on secure servers at Peter Mac. Only members of the research team will have access to this data, in accordance with the National Statement on Ethical Conduct in Human Research 2018 and the Australian Code for Responsible Conduct of Research 2018. Hard-copy data will be stored in locked filing cabinets within the Department of Psychosocial Oncology at Peter Mac. Five years after publication or dissemination of project outcomes, hard-copy and electronic data will be destroyed.

Anonymous data from the FCRI-SF and FCR-1 may also be shared with each measure’s author to assist in their ongoing validation of these measures. The data shared may also include anonymous demographic and medical information to describe the population from which the data is drawn. This data will be anonymized in a separate password-protected file; the password will be provided to the author separately to the emailed data file.

### Data analysis

#### Quantitative analysis

Quantitative data will be analyzed using SPSS (V.24).

##### Descriptive statistics

Descriptive statistics (e.g., count/percentage, mean/SD, median, interquartile range) will be used to summarise demographic, clinical and process data, responses to the FCRI-SF and FCR-1, and evaluation survey questions.

##### Feasibility

The feasibility of the stepped-care approach will be assessed by calculating percentages of survivors who completed screening, percentage of participants who consented to the interventions, percentage adherence to the interventions, and clinician time to deliver screening and interventions. The feasibility criteria (Table 2) are based on previous studies [11, 32, 42].

**Table 2 Tab2:** Feasibility criteria for *Fear-Less*

Outcome	Feasibility criteria
Screening rate	A majority (>60%) of survivors completing screening
Intervention uptake	A majority (>60%) of participants consenting to the intervention
Intervention adherence	• For those receiving the self-management resource, self-reported reading 75% of more of the booklet by two thirds of participants • For those receiving ConquerFear, completion of four or more sessions of the intervention

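### The single >60% uptake criterion in Table 2 is not split by step, so it can be met while only a minority of those offered ConquerFear accept it

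*Protocol article*

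**What the plan says.** The protocol article, under Feasibility, plans to calculate the "percentage of participants who consented to the interventions", and Table 2 turns this into one pass rule: "A majority (>60%) of participants consenting to the intervention". The adherence row of the same table has a separate line for each step; the ConquerFear line reads "For those receiving ConquerFear, completion of four or more sessions of the intervention".

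Table 1, under Process data, shows the same contrast. It lists "Number of survivors referred to each intervention", which is per step, but only one consent count, "Number of participants that consented to the intervention", placed at enrolment. The text there promises "referral rates for each intervention, and intervention uptake and adherence".

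Study procedures describes the route for people scoring 22 or more on the FCRI-SF. After a discussion with a psychologist, "Participants whose assessment indicates clinical levels of FCR will be offered ConquerFear". Two groups are diverted to the booklet: those judged sub-threshold, and those "who do not wish to take part in the ConquerFear therapy, will be offered the self-management intervention".

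**The concern.** Feasibility of *Fear-Less* is part of the primary aim. What distinguishes the model is that individual therapy is kept for people with clinical FCR, so whether those people accept it is a central feasibility question. No criterion in Table 2 answers it:

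- The screening rate is settled before any offer is made.
- The uptake line does not separate the steps.
- The ConquerFear adherence line covers only people who receive ConquerFear, so those who declined have already left its denominator.

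Most people with clinical FCR could therefore decline therapy without any stated criterion failing. The Discussion makes further efficacy and cost-effectiveness work depend on a favourable result, so a pass that says nothing about the high-intensity step could carry more weight than it should.

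**Working it through.** The protocol has no calculation to reproduce here: 60% is a bare threshold, and the sample of 60 rests on an earlier study, funding, resources and duration.

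**Inputs from the protocol.** 60 recruits; about 50% of survivors with moderate-to-high FCR (Background); uptake threshold above 60%.

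**Assumed inputs.** 30 of the 60 are offered an intervention (the 50% applied to the sample). The high/moderate split, the acceptance rates and the fallback rate are not in the protocol. For simplicity every high scorer is taken as offered ConquerFear, although some would be re-routed as sub-threshold.

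**Formulas.**
- Pooled uptake, fallbacks counted = (moderate acceptances + ConquerFear acceptances + decliners who take the booklet) / all offered
- Pooled uptake, first offer only = (moderate acceptances + ConquerFear acceptances) / all offered
- ConquerFear uptake = ConquerFear acceptances / offered ConquerFear

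**A. Fallbacks counted as consent.** Take 15 high and 15 moderate scorers, with 5 accepting ConquerFear, 10 declining and taking the booklet, and 12 moderate acceptances.
- Pooled: (12 + 5 + 10)/30 = 27/30 = 90%, pass.
- ConquerFear: 5/15 = 33%, below the benchmark.
- With no ConquerFear acceptances, 10 fallbacks and 12 moderate acceptances: 22/30 = 73%, still a pass.

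The first case assumes that every decliner takes the booklet. With about 70% of decliners doing so, 10 of 15 moderate acceptances and 3 of 15 accepting ConquerFear, 8 of the 12 decliners fall back. Pooled uptake is (10 + 3 + 8)/30 = 21/30 = 70%, pass; ConquerFear uptake is 3/15 = 20%.

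**B. Fallbacks not counted.** The first case in A becomes (12 + 5)/30 = 17/30 = 57% and fails, so the result now depends on the mix. Let *h* be the high-FCR share of those offered and *m* the moderate-step uptake. The pooled rule passes once ConquerFear uptake exceeds (0.60 − (1 − *h*)*m*)/*h*:
- *h* = 0.5, *m* = 0.8: (0.60 − 0.40)/0.5 = 40%
- *h* = 0.4, *m* = 0.8: (0.60 − 0.48)/0.4 = 30%
- *h* = 0.3, *m* = 0.8: (0.60 − 0.56)/0.3 = 13%

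A whole-number case: 9 high and 21 moderate scorers, 2 accepting ConquerFear and 17 moderate acceptances. Pooled uptake is 19/30 = 63%, pass; ConquerFear uptake is 2/9 = 22%.

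**C. Chance of passing.** Assumed true rates: 30% ConquerFear acceptance, 70% fallback among decliners, 70% moderate uptake. A high scorer then accepts something with probability 0.30 + 0.70 × 0.70 = 0.79. Exact binomial results with 30 offered and a high-FCR share of 30% to 60%:

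| Rule (>60%) | Probability of passing |
|---|---|
| Pooled, fallbacks counted | 0.91 to 0.96 |
| Pooled, first offer only | 0.03 to 0.33 |
| ConquerFear alone | 0.004 to 0.025 |

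**D. Denominator.** If Table 2 means all 60 recruits, the two pooled figures in A that use 12 moderate acceptances become 27/60 = 45% and 22/60 = 37%, and neither passes. With 30 offered, even full acceptance gives only 30/60 = 50%.

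**The case against.** A reader might infer that the protocol counts a ConquerFear refusal followed by the booklet as a success, and that this holds whatever denominator is used. The documents do not support either statement. The counting rule is nowhere given. Table 1 places the consent count at enrolment, and Study procedures puts consent before the psychologist discussion and the offer, so the count may precede any fallback. The singular wording in Table 2 could also mean the step offered. And, as D shows, the illustrative passes disappear if all 60 recruits form the denominator.

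A reader might also infer that refusals would be hidden. They would not be, for the most part: referrals to each step, numbers declining with reasons, and ConquerFear sessions completed are all collected and summarised.

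It is also fair to say that the booklet option is part of the model, so acceptance of any level is a defensible model-level measure. The protocol never claims that meeting the line shows uptake of ConquerFear. The split and rates used above are assumptions, and a threshold applied to about 15 people is imprecise. Exact numerators and denominators may also stand in a fuller document.

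These points limit the claim but do not remove it. Consent counted at enrolment says nothing about acceptance of ConquerFear. First-offer counting still allows a pass with minority uptake (B). Only a strictly per-step reading would detect refusal; the text does not give one, and the split adherence row and per-step referral count suggest that uptake was left pooled. Table 2 is the published pass rule, so the point concerns what it states rather than detail left elsewhere.

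**Conclusion.** The point holds as a weakness of the pass rule. As written, the uptake criterion can be met while a minority of those offered ConquerFear accept it, and no other criterion in Table 2 would show this. With those offered an intervention as denominator and fallbacks counted, the gap can be as wide as 90% pooled against 33% for ConquerFear. With fallbacks excluded it is smaller and depends on the case mix, for example 63% against 22%. These sizes show what the rule permits and do not predict the result. The change is worth making before the feasibility conclusion is drawn, because the conclusion concerns both steps and the data to assess each are largely collected already.

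**What to change.** In Table 2, define uptake by the step first offered:

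- ConquerFear uptake = people accepting ConquerFear / people offered it after the psychologist discussion.
- Booklet uptake = people accepting the booklet / people for whom it was the first step offered.

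Give each with an exact confidence interval and judge each against the >60% benchmark. A pooled model-level figure may be kept alongside, with its numerator and denominator stated. Count a ConquerFear decline followed by the booklet as non-uptake of ConquerFear, and report these people separately from those re-routed because they were judged sub-threshold.

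The cost is a wording change in Table 2 and a CRF code for step offered and step accepted. Nothing changes in what participants are offered. The downside is that the ConquerFear figure rests on few people and may look less favourable: 9/15, for instance, has an exact 95% interval of about 32% to 84%. The interval should therefore be read with the benchmark, and the comparison not treated as a sharp test.

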##### Impact

Change scores between pre- and post-intervention FCRI-SF will be calculated to describe the impact of the *Fear-Less* interventions. Participants who report a reduction of 10% or more on the FCRI-SF (indicative of a clinically significant improvement [43]) will be considered to have a reduction in FCR.

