## Background

Fear of cancer recurrence (FCR) describes the fear, worry, or concern cancer will come back or progress [1]. Approximately, 50% of cancer survivors experience moderate-to-high or clinically significant FCR [2, 3]. FCR involves intrusive thoughts, worries, hypervigilance to physical symptoms and either avoidance of, or excessive levels of symptom checking [1]. At clinical levels, FCR is characterized by high levels of persistent worry and hypervigilance or hypersensitivity to bodily symptoms [4] and has been associated with poor day-to-day functioning, reduced quality of life, and increased rates of depression, anxiety, and worry about the future [5]. It is often heightened prior to receiving scan results or attending medical reviews [6]. Untreated FCR has been related to the avoidance of or excessive requests for medical reviews, examinations, or follow-ups, potentially risking adverse health outcomes for survivors and increased health costs to survivors and health services [5, 7–9].

Over the past decade, several psychological interventions have been developed and trialled to address cancer survivors’ FCR [7, 10–17]. These interventions target attitudes, beliefs, and behaviors that may exacerbate or maintain FCR. In addition to significantly reducing levels of FCR, these interventions have led to improvement in emotional wellbeing [10, 11] and quality of life [10]. One intervention is ConquerFear, a five-session manualized treatment [10] developed based on a cognitive processing model of FCR [18]. The intervention targets key processes that contribute to FCR, including worry and excessive threat monitoring, unhelpful beliefs about worry, inappropriate monitoring and screening behaviors, and existential concerns [10]. Compared to a manualized relaxation intervention, ConquerFear was shown to reduce FCR in survivors with early-stage melanoma, breast cancer, or colorectal cancer, with reductions maintained at 6 months. Effects of ConquerFear were shown to be mediated by changes in metacognitions and intrusive thoughts about cancer [19]. ConquerFear was also considered by clinicians to be a sustainable intervention in routine practice [20] and likely cost-effective [21].

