## Methods

### Study design

This study is a single-arm evaluation study which will assess the feasibility, acceptability, and impact of *Fear-Less*. The study adheres to the SPIRIT checklist (see Additional File 1).

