##### Recruitment and consent

Participants will be recruited from the breast, gynecology, and head and neck clinical services at Peter MacCallum Cancer Centre (Peter Mac), Royal Melbourne Hospital, and Royal Women’s Hospital in Melbourne, Australia. Survivors will complete FCR screening measures (described below) as part of their routine care, for example, during an appointment with their oncologist or by nursing staff completing survivorship care.

Survivors who complete screening and meet the above inclusion criteria will be identified by clinical staff supporting the *Fear-Less* program, such as their oncologist or nurse. These survivors will be provided a leaflet informing them about the *Fear-Less* program and that they will be contacted by a member of the research team. These survivors will then be invited to participate in the evaluation of the stepped-care approach by a member of the research team.

If the survivor is interested in participating, they will be provided with verbal and written information about the project, including the Participant Information and Consent Form (PICF). Consent will be obtained either via an online form or paper form returned using a reply-paid envelope.

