## Discussion

Approximately 50% of cancer survivors experience moderate-to-high levels of FCR [2, 3], which left untreated, are associated with poorer health outcomes [5, 7–9]. Support for FCR remains a significant unmet need for cancer survivors, where systemic barriers to identifying and treating FCR include lack of routine screening and limited resources to provide interventions for individuals experiencing FCR [22, 23]. Specific strategies, such as a stepped-care approach and the refinement of interventions included in this approach, may provide a solution to these barriers [26].

The *Fear-Less s*tepped-care model provides a framework for screening FCR and stratifying survivors to the appropriate level of treatment, so that the more intensive ConquerFear is reserved for individuals with clinical FCR. This is a novel model of care that has shown promising outcomes with a stage IV melanoma population [32]. Our study will provide an indication of whether this model is also feasible and acceptable amongst early-stage cancer survivors.

Additionally, our study will contribute to the growing literature regarding less intensive FCR interventions. As described by Pradhan et al. [26], there are currently few minimal interventions for FCR that can be implemented within a stepped-care approach. The outcomes from our evaluation will provide an indication of whether our purpose-developed self-management resource is acceptable and feasible to participants and improves FCR levels.

Should this be the case, further investigations regarding the efficacy and cost-effectiveness of *Fear-Less* can be conducted.

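### The screening FCRI-SF score that allocates people to treatment is also the only pre-treatment score, so the uncontrolled change leans towards improvement, mainly in the ≥22 group

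*Protocol article*

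**What the plan says.** The Study design section describes the trial so: "This study is a single-arm evaluation study which will assess the feasibility, acceptability, and impact" of the programme. Under Study procedures, consenting survivors "will be stratified into a specific level of care within the stepped-care program based on their screening score on the FCRI-SF". The booklet is for "moderate/subthreshold levels of FCR (score of 13–21 on FCRI-SF") and ConquerFear is for scores of 22 or more, each after a discussion with a psychologist. Of people scoring below 13 the article says: "No further follow-up or additional screening will be undertaken for these participants".

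Table 1 lists the FCRI-SF and the FCR-1 before enrolment and after the intervention, and at no other time. At enrolment it lists only the Screening Survivor Experience Survey as a questionnaire.

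The Impact section states that "Change scores between pre- and post-intervention FCRI-SF will be calculated to describe the impact" of the interventions, and counts a fall of at least 10% as a reduction in FCR.

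On timing, Recruitment and consent says: "Survivors will complete FCR screening measures (described below) as part of their routine care, for example, during an appointment with their oncologist"; nursing staff completing survivorship care are the other example. The Background says of FCR: "It is often heightened prior to receiving scan results or attending medical reviews". The Discussion expects the outcomes to indicate whether the booklet "is acceptable and feasible to participants and improves FCR levels".

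**The concern.** A group chosen because its scores on one occasion were high will, on average, score lower on the next occasion even if nothing has been done. Here the selecting score is also the baseline of the change score. There is no control arm, and people below 13 are not measured again, so the study produces nothing that separates this drift from a treatment effect. An analysis plan cannot fully repair it, because a second pre-treatment score that was never collected cannot be recovered.

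A second influence may act in the same direction. If the screening score is taken around a medical visit, the Background's own statement implies that it may be temporarily raised.

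At stake are the description of impact, the share counted as having a reduction in FCR, and the Discussion's statement about the booklet.

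**Working it through.** The plan gives no figure to reproduce: the sample of 60 rests on precedent and resources. The check is what the change score would show with no treatment effect.

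**Inputs from the article**
- Cut-offs 13 and 22 (Study procedures); score range 0–36 and retest correlation r = 0.89 (FCR assessments).
- About 50% of survivors have moderate-to-high FCR (Background). This puts the screened mean near 12.5 if 13 is the lower cut.
- Responder rule: a fall of at least 10% (Impact).

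**Assumptions (not in the article)**
- Screened mean 12.5 to 14, SD 6 to 9, roughly normal scores rounded and limited to 0–36.
- r also at 0.80 and 0.70, because the interval behind 0.89 is not stated.
- Selection on the score alone.

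**Formula**

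Expected fall with no effect = (1 − r) × (mean pre score of the band − screened mean).

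**Mean 12.5, SD 8, r = 0.89**
- ≥22 band, mean pre score 25.5: 0.11 × (25.5 − 12.5) = 1.43 points (simulated 1.44–1.46).
- 13–21 band, mean pre score 16.6: 0.11 × (16.6 − 12.5) = 0.45 point (simulated 0.45).

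**Ends of the range at r = 0.89**
- ≥22: lowest at mean 14, SD 6: 0.11 × (24.4 − 14) = 1.14 (simulated 1.16). Highest at mean 12.5, SD 9: 0.11 × (26.2 − 12.5) = 1.51 (simulated 1.53).
- 13–21: 0.11 × (16.5 − 14) = 0.28 up to 0.11 × (16.6 − 12.5) = 0.45 (simulated 0.28 to 0.47).

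**Simulated results with no treatment effect, mean 12.5–14, SD 6–9**

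| r | Mean fall, 13–21 | Mean fall, ≥22 |
|---|---|---|
| 0.89 | 0.3–0.5 | 1.2–1.5 |
| 0.80 | 0.5–0.8 | 2.1–2.8 |
| 0.70 | 0.7–1.2 | 3.1–4.1 |

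At r = 0.89, 31–39% of the ≥22 band fall by at least 10% and 8–16% rise by at least 10%. In the 13–21 band the shares are 32–39% and 24–32%, which is much closer to balance.

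**Visit effect**

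The article gives no size. If the visit raises the screening score by some amount that has gone by the post score, the fall grows by about that amount. At mean 12.5, SD 8, r = 0.89, an assumed 1 point takes the falls to 1.4 (13–21) and 2.4 (≥22). This only returns the assumption and is no estimate.

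**With a repeat pre score not used for selection**

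The mean change with no effect is 0.0 within simulation error in both bands. At mean 12.5, SD 8, r = 0.89, the share with a 10% fall goes from about 38% to 33% in the 13–21 band (35% rise) and from 37–38% to 25% in the ≥22 band (27% rise).

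**The case against.** The strongest reply is that impact is a modest part of the study. The primary aim is acceptability and feasibility, impact is called preliminary, no test is planned, and no criterion in Table 2 uses FCR change. The Discussion leaves efficacy to further work. This stands, and it limits the point to how the change is described.

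The Discussion's statement also concerns the booklet, whose main recipients score 13–21, where regression is small. This stands too, with one reservation: people scoring ≥22 who are judged sub-threshold or decline ConquerFear are offered the booklet and carry their high screening score into that group. The psychologist's discussion means that the intervention groups do not match the score bands exactly, and the net effect is not quantified here.

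A reader might infer that the pre score is known to be inflated by the clinic visit and the post score is known to be taken away from one. The documents do not support that. The oncologist appointment is only an example, the Background speaks of the time before reviews, and the phone, mail and email contacts are reminders for unreturned questionnaires. Post scores may also fall near visits.

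A reader might also set the 1.2–1.5 point fall against the 2.5 points that 10% represents at a score of 25. That compares a group mean with a cut-off for individuals. The fair comparison is the share falling against the share rising.

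Finally, an article condenses a fuller protocol. But Table 1 sets out the schedule of measures explicitly, and the score that selects is the only one before the intervention.

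**Conclusion.** The point holds in a limited form. The selecting score is the only pre-intervention score, so with no control the change score and the 10% responder share are biased towards improvement. At the article's r = 0.89 the bias is about 1.2–1.5 points in the ≥22 band, with a clear imbalance between chance falls and chance rises, and about 0.3–0.5 point in the 13–21 band. These sizes rest on the assumed mean and SD and on selection by score alone. They grow if the correlation over the actual interval is below 0.89. Any visit-related elevation would add to them, but its size and how many people it affects are unknown.

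It would go too far to infer that an observed improvement must be artefact, or that the booklet result is dominated by regression: at r = 0.89 the figures for the 13–21 band do not show that. The feasibility and acceptability conclusions do not depend on the change score.

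**What to change.** Keep the screening score for allocation only. Re-administer the FCRI-SF and FCR-1 after consent and before the intervention, together with the Screening Survivor Experience Survey, which all participants already receive at that point. Add the entries to Table 1 under enrolment, and compute the change and the 10% rule from the repeat score.

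Repeating the measures in low-FCR participants is optional. It would help to show the drift between screening and enrolment, but the sentence in Study procedures that rules out further screening for them would have to be aligned.

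If no repeat score can be added, report the observed change beside (1 − r) × (group mean − screened mean), using the study's own means, with r = 0.89 and lower values. In the Impact section and the Discussion, word the result as uncontrolled change rather than as impact or improvement due to the booklet.

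The cost is ten more items (nine plus one) at an existing contact and a minor amendment. The extra items are some burden in a study that itself names questionnaire length as a barrier. The repeat score does not remove chance responders under the 10% rule or natural decline over time, so reporting the share with a 10% increase beside the share with a 10% reduction would help the reader.
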